### Analysis strategy

For evaluating the effectiveness of clinical audits in reducing NMIC rates, the unit of analysis is the patient. The main tests will be intention-to-treat analyses. A first descriptive analysis will be done to verify group comparability in terms of the characteristics of hospitals and patients included in the pre-intervention period. The primary analyses will take into account inter- and intra-cluster variability. We will use generalized estimating equations (GEE) to adjust the variance estimation for the intervention’s effect on inter-dependence of the measured events (NMIC or not) among patients of the same hospital [79]. The exchangeable structure of the residual covariance matrix will be used to represent the intra-cluster correlations. The same approach will be used to test the effectiveness of CBCAs in relation to resource improvement (complexity score), medical practices (caesarean quality score), and reductions in maternal and perinatal mortality. The intervention’s effect on the NMIC rate will be estimated from the odds ratio (95 % CI) based on the GEE approach and tested with the two-sided Wald test (α = 0.05) [79]. The intervention’s effects will be evaluated systematically both without adjustment and with adjustments on the stratification variables (type of hospital) and on the other baseline characteristics selected a priori, whose distribution could, even with randomization, be unbalanced between the two groups.

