Preliminary analyses will test whether the intervention’s effects vary according to hospital type, using chi-squared likelihood ratio tests with 2 degrees of freedom for hospital–intervention interaction. If the test does not reject the null hypothesis with α = 0.05, the interactions will be eliminated from the final model, which will enable the overall effect of the intervention to be estimated. However, if the interactions are statistically significant, subgroup analyses will be done to estimate the effects of the intervention separately for each type of hospital (district vs. regional), with a power of less than 90 %. A similar approach will be used to test whether the intervention’s effects depend on: 1) the caesarean rate in the pre-intervention period; 2) the initial knowledge score in the pre-intervention period; or 3) patient characteristics (age, parity, previous caesarean, prenatal care, referral for delivery) and any other variables distributed unevenly among groups in the pre-intervention period. In all secondary analyses, the intervention’s effects will be estimated from the adjusted odds ratio using the GEE approach, which generalizes the logistic regression to clustered data [79]. To analyze the implementation and heterogeneity of effects, interviews will be fully transcribed into a word processor program. Subsequently, qualitative data will be coded and organized using QDA Miner software and then subjected to content analysis [80].

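### The interaction plan moves from the overall effect to subgroup effects on p < 0.05, covers eight named modifiers, and adds without limit any variable unbalanced at baseline

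*Protocol article*

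**What the plan says.** All of this is in the Analysis strategy section of the protocol article.

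- **Hospital type.** "Preliminary analyses will test whether the intervention’s effects vary according to hospital type", by a likelihood ratio test on 2 degrees of freedom.
- **If not significant.** "If the test does not reject the null hypothesis with α = 0.05, the interactions will be eliminated from the final model", and the overall effect is then estimated.
- **If significant.** "if the interactions are statistically significant, subgroup analyses will be done to estimate the effects of the intervention separately" for each hospital type. The plan concedes that power for these estimates is below 90%.
- **Extension.** "A similar approach will be used to test whether the intervention’s effects depend on: 1) the caesarean rate in the pre-intervention period". The list goes on to the baseline knowledge score and to five patient characteristics: age, parity, previous caesarean, prenatal care and referral.
- **Open end.** The list closes with "any other variables distributed unevenly among groups in the pre-intervention period". The text neither defines unevenness nor limits how many variables may enter this way.

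The paragraph before treats imbalance differently. There, the possibility of chance imbalance is a reason to adjust, and the adjustment variables are to be chosen in advance.

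**The concern.** Two features of the stated rule are unsound.

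First, the open clause selects effect modifiers by baseline imbalance. Under randomisation an imbalance is a chance event. It may justify adjustment, because an unbalanced prognostic variable can shift the estimate. It says nothing about whether the effect differs across levels of that variable. The clause therefore adds tests for a reason unrelated to effect modification. It also leaves their number unknown until the baseline data are examined, so no per-test level set in advance could control the error over the whole set.

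Second, a significance test decides what is reported. For hospital type, p < 0.05 moves the analysis from one overall effect to separate effects, and the natural reading is that the other modifiers follow suit. The more tests are run under such a rule, the more often a common effect is presented as heterogeneous.

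The consequence matters here. The Hypotheses section expects any heterogeneity to be explained by hospital context, and the qualitative work is designed to explain it. A false interaction would readily acquire an explanation. The Discussion section says control hospitals will be offered the intervention if it is shown to work, so a spurious subgroup result could influence where it goes.

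**Working it through.** **Inputs, all from Analysis strategy**

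- Level of each interaction test: 0.05, stated for hospital type and read across to the others.
- Named modifiers: hospital type (1) + pre-intervention caesarean rate (1) + baseline knowledge score (1) + patient characteristics (5) = 8. The hospital-type test has 2 degrees of freedom but is one test at 0.05.
- Added unbalanced variables: number not stated.

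The plan gives no error rate for the set of interaction tests, so there is no figure to reproduce. The calculation assumes a common effect (no true interaction) and tests that hold their nominal size.

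**Independent tests.** P(at least one false interaction) = 1 − (1 − 0.05)^k.

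| Tests k | Unbalanced variables added | P(at least one) |
|---|---|---|
| 1 | hospital type only | 5.0% |
| 8 | 0 | 1 − 0.95^8 = 33.7% |
| 10 | 2 | 40.1% |
| 13 | 5 | 48.7% |
| 14 | 6 | 51.2% |

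The expected number of false interactions among the eight is 8 × 0.05 = 0.4. Passing 50% requires 0.95^k < 0.5, that is k > ln 0.5 / ln 0.95 = 13.5. So at least 14 tests are needed, six beyond those named.

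**Correlated tests.** The statistics may be correlated, for example those for age and parity. With eight equally correlated standard normal statistics, each tested two-sided at 0.05 (400,000 draws):

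| Correlation | P(at least one) |
|---|---|
| 0 | 33.7% |
| 0.2 | 31.9% |
| 0.3 | 30.0% |
| 0.5 | 24.9% |

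**Scale of the open clause.** Holding 5% over the eight named tests by Bonferroni would need 0.05 / 8 = 0.00625 per test. Once the list is open, that divisor is undefined.

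**The case against.** The case against has several parts.

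*The switch is written out for hospital type only.* This stands as a matter of wording. For the other modifiers it is an inference from the reference to a similar approach, though a natural one. The preceding paragraph also promises effects with and without adjustment, with no condition about interactions. A reader might infer that the overall effect would go unreported after a significant interaction, but the documents do not clearly say so. They leave it unsettled.

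*Multiplicity for secondary tests is commonly left to an analysis plan.* This also stands, and absence of a multiplicity procedure is not the point. The imbalance clause and the test-then-subgroup rule are stated choices, and an analysis plan that followed them would inherit both.

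*Baseline imbalance is visible before post-intervention outcomes exist.* True: the open list is not driven by outcomes. Its faults are that its length is not fixed and that its selection criterion is irrelevant to effect modification.

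*Heterogeneity is a declared aim.* That justifies examining modifiers. It does not justify choosing them by imbalance, or letting a test decide whether the overall effect leads the report.

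Two stronger readings are tempting. One is that a false subgroup finding is more likely than not. A simulation of 22 hospitals with 100 records each did give at least one false interaction in about 64% of runs (ICC 0.02, rates of 24% and 12%, an assumed 8/4/10 split by hospital type, uncorrected cluster-robust Wald tests). The excess over 34% comes from inflated size of the individual tests with few clusters: about 25% for hospital type, 14–15% for hospital-level covariates and 7–8% for patient-level ones. It does not come from the number of tests or the imbalance clause. The plan names a likelihood ratio test for interaction, the documents do not give the split, and a small-sample correction may be set in an analysis plan not shown. The other reading is that several variables will qualify as unbalanced. That cannot be shown without a candidate list or a threshold.

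**Conclusion.** The point holds in limited form. The plan states a poor rule: it admits interaction tests on the strength of chance imbalance, leaves their number open, and lets a significant result move the report from the overall effect to subgroup effects. With a common effect, the eight named tests carry a nominal chance of at least one false interaction of 34% if independent, or about 25–32% at correlations of 0.5 to 0.2. The chance rises to 40% with two added variables and exceeds 50% only with six or more.

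These figures assume independent or equally correlated tests that hold their 5% size, and a 0.05 level for all eight, which the text states outright only for hospital type. The primary test of the intervention effect is not itself at fault here. What is exposed is how the result is presented and interpreted. The flaw should be corrected, but it does not invalidate the trial.

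**What to change.** Three changes to the second paragraph of Analysis strategy:

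1. Delete "any other variables distributed unevenly among groups in the pre-intervention period", with the conjunction before it, from the list of modifiers to be tested. Use such variables at most in a labelled sensitivity adjustment.
2. State that the overall intervention effect is always estimated and reported as the primary result, whatever any interaction test shows. This must include hospital type, since that is where the switch is written out.
3. Label all interaction and subgroup results exploratory, and report them with the number of interaction tests done.

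A formal multiplicity adjustment across the exploratory tests is optional once these are in place.

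The cost is a few sentences. Subgroup findings will carry less weight, but the plan already concedes reduced power for the hospital-type subgroups, and no data collection or sample size changes.

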### Type of analysis and treatment of hospitals lost to follow-up

We believe the acceptability of the various components of the intervention, including the caesarean audits, is high [34, 35]. Nevertheless, some hospitals may decide to withdraw from the study. For these hospitals, data collection will continue until the end of the study, in accordance with the commitment made by the hospital authorities at the time of inclusion. These hospitals will therefore not be excluded from the analysis. In accordance with the intention-to-treat analysis approach, every patient will be analyzed at the hospital where she was admitted, and each hospital will be analyzed in the group to which it was randomly allocated.

There is no data monitoring committee and no stopping rules.

### Potential limitations of the trial

Although there is no intervention planned as part of this study in the control group, activity related to data collection may have an impact on improving the practice of caesareans. However, this data collection effect is, a priori, similar in both groups (intervention and control). The results of our trial could be contaminated if there is a transfer of staff from intervention hospitals to control hospitals. Such contamination could reduce the apparent effectiveness of the intervention. To assess the extent of this potential contamination, we will keep track of all personnel transfers between hospitals of the two arms of the trial. It should be noted, however, that implementing the components of the intervention requires sustained teamwork and is unlikely to be accomplished by isolated individuals. We also plan to study in depth the events and environments of all hospitals in the control group. As the subsidy for emergency obstetric and neonatal care was passed until 2015, a decision not to extend it into 2016 could also limit this study.

**Start of study:** May 2, 2014

**Intervention period:** May 2015 to April 2016.

**End date:** November 2016

## Discussion

While greater access to caesareans is a necessity in countries where the national rate is below 10 % [10], it is imperative that quality improvement programs are implemented at the same time to prevent excessive and inappropriate increases in caesarean rates [11]. High rates of non-medically indicated caesareans (NMIC) are associated not only with adverse health outcomes for mothers and infants, but also with high public spending on health, presenting equity and efficiency challenges for low-resource countries [12–19].

Various strategies for reducing the proportion of NMICs have been tested and evaluated, while the results of some observational studies carried out in sub-Saharan Africa are promising [27], and the results of randomized controlled trials in high-income countries are encouraging [25], we found no evidence that these strategies are effective in reducing NMIC rates in low- or middle-income countries, nor on their large-scale implementation. For this reason, we think that this trial is relevant in the context of Burkina Faso where fees for caesarean delivery were partially removed in 2006, and then totally removed in 2016.

This study will provide evidence regarding the effectiveness of a multi-faceted intervention for reducing non-medically indicated caesareans in a low-income country. Although there is no “intervention”, the activity related to data collection may have an impact on labour and delivery management and on the indication of caesarean deliveries in the control group. However, this “data collection” effect is a priori similar in the two groups (intervention versus control). Furthermore, the implementation of audit activities may vary between hospitals and then the effect of the intervention may be different in various settings. By combining qualitative and quantitative methods, the study’s findings will allow understanding the factors that could influence the intervention process and ultimately the intended outcomes. The results of this study will be shared with health professionals and decision-makers in Burkina Faso and may also interest others low-income countries where the policy of user fees removal has been implemented and where indications for caesareans are not only assessed by obstetricians.

Participating hospitals were included on the basis of informed consent given by local authorities (hospital director and maternity service chief). The authorities were informed that: 1) all hospitals are free to withdraw from the project at any time; 2) the intervention will be offered in hospitals in the control group at the end of the study if proven effective; and 3) data collection will continue until the end of the study, even for hospitals that withdraw from the study. The collection of clinical data from hospital registers and medical records has been authorized by the hospital administrations and does not require patient consent [73].

All information collected on patients, health professionals, and health facilities is confidential. Access to the clinical database is restricted to the data manager until the end of the study. Access to the other databases is restricted to the researchers in charge of the study. For this study, interviews and observations will be conducted, and informed consent will be sought from all participants by means of information sheets, which they will sign. Given the variety of research activities, various types of information sheets will be developed. Consent will be certified in writing.

## Abbreviations

CBCA: Criteria based clinical audit
CEPED: Centre Population et Développement
CS: Caesarean section
ESPUM: University of Montreal School of Public Health
IRD: Institut de Recherche pour le Développement
IRSPUM: University of Montreal Public Health Research Institute, Montreal, Canada
IRSS: Institut de Recherche en Sciences de la Santé
NMIC: Non-medically indicated caesarean section
